#### Child intake of indicator foods

Dietary indicator foods (fruit, vegetables and energy-dense products), will be measured using the diet portion of a validated parent proxy questionnaire, the Eating and Physical Activity Questionnaire (EPAQ) [63], which was translated into Swedish and adapted to the Swedish context as reported previously [34]. Parents who consented to be included in the study will be asked to recall the child’s intake (servings/day) of selected foods (snacks, sweets/chocolate, ice cream, cakes/buns/cookies, fruits, vegetables, soft drinks, flavoured milk and fruit juice) during the previous day, which should be a weekday. Aggregated variables will be analysed indicating unhealthy foods (snacks, sweets/chocolate, ice-cream, cakes/buns/ cookies), healthy foods (fruit and vegetables) and unhealthy drinks (soft drink, flavoured milk and fruit juice) to analyse food patterns. The parents will be asked to answer the questionnaire at three timepoints, at baseline, at the end of the first school year, and 12 months after that.

#### Parent outcomes

Parents will receive a link by e-mail to answer online questionnaires, alternatively on paper. At baseline they will answer questions regarding their sex, educational level, country of birth, and towards the end of the school year also their responsiveness to the program components (Table 4). In total three reminders will be sent out via e-mail or text message.

##### Diabetes risk test

All parents will be encouraged to complete the T2D risk test (FINDRISC) (0–26 points) at three timepoints (at baseline and end of the first school year, and again after 12 months), in the health information brochure or on the national health care website (www.1177.se) and will receive feedback regarding their level of risk. Parents who have consented to the study will send their results to the research team using an online form.

##### Parental feeding practices

Parental feeding practices, including modelling, will be measured using the Comprehensive Feeding Practices Questionnaire (CFPQ) developed by Musher-Eizenman, covering both positive and negative practices, and validated in a middle-income US sample [64]. We will use the Swedish short version with 36 items. The questionnaire will assess the parental feeding practices of involvement, environment, food restriction for weight control, restriction for health reasons, encouragement of balance, pressure to eat, monitoring, emotion regulation, food as a reward, and modelling. The parents are asked to answer the questionnaire online at three timepoints, at baseline, at the end of the school year, and 12 months after that (Table 5).

**Table 5 Tab5:** Outcome, moderators, and time of data collection

Indicator	Time of data collection			
	2021	2022	2023	2024
School characteristics	June			
Parents’ demographic data Fidelity to HSS components	October (C1)	October (C2) June (C1)	June (C2)	
Acceptability	September	June	June	June
Appropriateness	September	June	June	June
Feasibility	September	June	June	June
Organisational readiness	September	June	June	June
Fidelity to implementation strategies		May	May	May
Child height and weight	December (C1)	December (C2)	December (C1)	December (C2)
Child diet	October (C1)	June (C1) October (C2)	June (C1 + C2)	June (C2)
Parents’ T2D risk	October (C1)	June (C1) October (C2)	June (C1 + C2)	June (C2)
Parental feeding practices	October (C1)	June (C1) October (C2)	June (C1 + C2)	June (C2)

*C* cohort of children

### Stakeholder interviews

Experiences and satisfaction with the program, how it is being implemented, and how to achieve sustainability of the HSS will be assessed through in-depth interviews with a purposeful sample of nurses, school principals and representatives from the municipality management and primary health care in the latter part of the study. Semi-structured interview guides will be constructed for each target group. Interviews will be transcribed verbatim, coded and analysed using an inductive approach of content analysis [65, 66].

### Data management and statistical analysis

Data collection will be performed in a secure web platform Research Electronic Data Capture (REDCap) for building and managing online databases and surveys [67, 68]. All data will be stored electronically in password-protected folders on a secure data server with systematic back-up routines at Karolinska Institutet to avoid unauthorized access. Folders containing raw data will be stored separately from the data being used in the analysis. Access to data will be restricted to the research personnel working directly with data entry or analyses. A detailed statistical analysis plan will be developed in collaboration with an academic statistician prior to the start of data analysis.

Baseline characteristics at both school and individual level will be cross-tabulated for group 1 and 2 to check for balance and to provide an overview of the study population. Continuous and normally distributed variables will be represented as mean, standard deviation and range. Non-normally distributed variables will be represented as median and interquartile ranges, and categorical variables will be presented as frequencies and percentages in each category.

Assessment of the primary outcomes adherence score and responsiveness score after 12 and 24 months will be performed on the individual level. Between-group effects in the adherence score (0–4) will be analyzed using ordinal logistic regression. Between-group effects in the responsiveness score (4-20) will be analyzed using mixed linear regression. The following factors will be explored as potential moderators of fidelity to intervention: school size, fidelity to implementation strategies, baseline organisational readiness, parent educational level and country of birth.

In order to answer the question of whether implementation of the HSS program at scale reduces social disparities in child weight status parent’s T2D risk we will do as follows. The secondary outcomes analysed will be the change in prevalence of child overweight and obesity, children’s sex and age-adjusted BMI and parents’ risk of T2D. Dichotome outcomes will be analysed with a logistic regression model and continous outcomes with linear or quantile regression models. We will use a method able to account for the within-school and within-person clustering such as mixed models or generalised estimation equations (GEE). Parent country of birth and child sex will be explored as moderators of child and parent outcomes in addition to intervention fidelity and other school-related factors mentioned above.

Effects of implementation strategies on primary and secondary outcomes within-group will be assessed yearly relative to baseline using repeated measures analyses. All analyses will be conducted on an intention-to-treat basis. Sensitivity analysis will be carried out for primary and secondary outcomes after imputing relevant missing data, if relevant.

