**Methods:**

IMPROVE is a cluster-randomized controlled trial with two arms to evaluate and compare the effects of two different bundles of implementation strategies on intervention fidelity expressed as adherence and responsiveness at 12 and 24 months (primary outcomes). Thirty schools in two municipalities will participate in the study reaching about 1400 families per school year. In stakeholder workshops, key implementation determinants were identified according to the domains of the Consolidated Framework for Implementation Research. Through a consensus process with stakeholders, two bundles of implementation strategies were tailored to address context-specific determinants. Schools randomly assigned to group 1 will receive bundle 1 (Basic) and group 2 will receive bundle 1 + 2 (Enhanced). Bundle 2 consists of external facilitation, fidelity monitoring and feedback strategies. Secondary outcomes will include change in acceptability, appropriateness, feasibility, and organisational readiness as perceived by school staff. In addition, child weight status and diet, and parents’ feeding practices and risk of type 2 diabetes will be monitored. Linear and ordinal regression analysis will be used to test the effect on the primary and secondary outcomes, taking clustering and covariates into consideration where needed. Process evaluation will be conducted through key stakeholder interviews to investigate experiences of the program and perceptions on sustainability.

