## Methods

### Study design

A hybrid type 3 cluster-randomized implementation effectiveness trial with 2 parallel arms (Basic and Enhanced) will be conducted (Fig. 1). Hybrid type 3 trials experimentally test the effects of implementation strategies on implementation outcomes while also gathering data on the effects on service recipient outcomes [45]. The primary dependent variable will be fidelity to the HSS (implementation outcome). Using a hybrid type 3 design is advantageous when (a) there is a high momentum and mandate for implementation despite a somewhat limited evidence base, (b) effects are suspected to be vulnerable to a “voltage drop” when scaling up into routine practice, and c) the implementation strategies being tested are reasonably feasible in context [45]. Figure 1 shows the program theory of IMPROVE using the evaluation model by Proctor et al. [46].

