### Randomisation and blinding

Within each municipality, schools will be randomised 1:1 to group 1 (Basic: bundle 1) or group 2 (Enhanced: bundle 1 + 2) using a computer-generated assignment by an independent statistician after baseline measurement has been conducted in September 2021. It is not possible to blind school staff and the research team to allocation, but parents and children will not get this information. The CONSORT flow diagram with the number of schools and children is shown in Fig. 2.

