### Primary outcome

Fidelity to the four components of the HSS will be assessed through 13 indicators (Table 4) based on the dimensions adherence, dose, participant responsiveness, and quality of delivery [56, 57]. This information will be gathered through attendance logs, questionnaires answered by school staff and parents, and audio recordings of MI sessions. The primary outcome will be operationalized as an adherence score and a responsiveness score to the four intervention components. Adherence to three of the four components will be reported by parents and the nurse as yes/no. The classroom component will be reported by the teachers, and thus the score for this component will be the same for all children in the same class. The total adherence score will be from 0 to 4. Participant responsiveness measures how parents respond to and are engaged in the intervention and is measured on a scale from 1 to 5 (no appreciation to full appreciation) for each component with a total score of 4 to 20. Dose refers to exposure or the amount of the classroom component that has been delivered and received. This information will be obtained from the teachers who will use a logbook to report the proportion of teaching sessions performed, the proportion of lesson completion including length, and whether any adaptations and are made. Quality refers to the MI component. All MI sessions will be recorded and a random 10% of each nurses’ interviews will be coded for MI competence using the MITI protocol 4.2 [58] by reliable coders. Those indicators not included in the two primary outcomes will be tested separately between the Basic and Enhanced group of schools.

**Table 4 Tab4:** Indicators of fidelity to the HSS components

Component	Adherence (%) (yes/no)	Dose (%)	Participant responsiveness (scale 1–5)	Quality of delivery
Brochure with health information	Parents reading the brochure (P)^a^	NA	Parents’ appreciation of the brochure (P)^b^	NA
Motivational Interview (MI)	Parents receiving MI (N)^a^	NA	Parents’ appreciation of health counselling (P)^b^	Quality of MI score coded according to MITI 4.2 (C)
Classroom component	Teachers providing the classroom component (T)^a^	Proportion of classroom lessons performed (T) Proportion of lesson completion (T)	Teachers’ perceived child involvement and engagement (T) Parent’s appreciation of the homework (P)^b^	NA

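### The primary adherence score is given an ordinal logistic model with no school clustering, while the other primary outcome gets a mixed model; taken literally, the test can reject well above 5% under the null

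*Protocol article*

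**What the plan says.** The unit of randomisation is clear: "Within each municipality, schools will be randomised 1:1" (Randomisation and blinding), and 30 schools take part (Abstract, Methods).

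The adherence score runs from 0 to 4, one point per component. The classroom item is reported by the teacher, and "thus the score for this component will be the same for all children in the same class" (Primary outcome).

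The section on data management and statistical analysis places the assessment of both primary outcomes at the level of the individual and names two models in adjacent sentences. For adherence: "Between-group effects in the adherence score (0–4) will be analyzed using ordinal logistic regression". For responsiveness: "Between-group effects in the responsiveness score (4-20) will be analyzed using mixed linear regression".

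Two other places bear on clustering. The abstract says that linear and ordinal regression will be used for primary and secondary outcomes, "taking clustering and covariates into consideration where needed". The analysis section also promises a method that handles correlation within schools and within persons, with mixed models and GEE as examples. That promise comes in the later paragraph on social disparities, after the secondary outcomes for that question are listed.

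**The concern.** In a school-randomised trial, parents in the same school are not independent observations of the arm effect. An ordinal logistic model fitted to individual parents without a school term or a cluster-robust variance treats them as independent. Its standard error for the arm effect is too small whenever scores correlate within school or class.

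For adherence that correlation is partly structural. If a teacher does not deliver the classroom component, every child in the class loses the same point. A second item, receipt of the motivational interview, depends on the school nurse, so correlation within schools is plausible there too.

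The protocol writes the mixed model into one primary outcome and leaves it out of the other, so an analyst who follows the text would run an unclustered test on the first-named primary outcome. At stake is a false-positive finding that the Enhanced bundle improves adherence.

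**Working it through.** **The plan's own power figures.** For responsiveness, with 400 parents per arm and SD 8, SE = 8 × √(2/400) = 0.566. Power = Φ(δ/SE − 1.96) for δ = 0.8, 1.6 and 3.2 gives 0.293, 0.807 and 0.9999, against the stated 0.29, 0.81 and 0.99. These reproduce with no allowance for clustering.

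For adherence, the stated 0.44, 0.66 and 0.86 at log odds ratios of 0.3, 0.4 and 0.5 imply an SE of about 0.166. The proportional-odds approximation is V = (N/12)(1 − Σp³) with N = 800. Five equal categories give V = 66.7 × 0.96 = 64, SE = 0.125 and power 0.67, 0.89 and 0.98. The stated figures fit equal categories with a design effect of about 1.76, or independent data with about 77% of parents in one category. The protocol states neither, so these figures do not show whether clustering was allowed for.

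**Inputs for the error rate.** From the protocol: 30 schools (taken as 15 per arm), 400 parents per arm, and one class-constant item out of four. Assumed, because not given: 2 classes per school with 13 analysed children each (400/15 ≈ 27 per school), the other three items independent with rates of 75%, 85% and 40%, and a two-sided 5% test.

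**Correlation from the shared item alone.** The variance of the three individual items is 0.75×0.25 + 0.85×0.15 + 0.40×0.60 = 0.1875 + 0.1275 + 0.24 = 0.555. If a share p of classes delivers the component, class ICC = p(1−p)/[p(1−p) + 0.555]. The design effect is 1 + 12 × ICC, and an unclustered test rejects approximately 2[1 − Φ(1.96/√DE)] of the time. The last column is from null simulation of the proportional-odds score test (the rank test with ties).

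| Classes delivering | ICC | Design effect | Approximate rejection | Simulated rejection |
|---|---|---|---|---|
| 100% | 0 | 1.00 | 5% | 5% |
| 98% | 0.034 | 1.41 | 10% | 7% |
| 95% | 0.079 | 1.95 | 16% | 14% |
| 90% | 0.14 | 2.67 | 23% | 22% |
| 80% | 0.22 | 3.69 | 31% | 29% |
| 70% | 0.275 | 4.29 | 34% | 36% |

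The approximation is crude near full delivery: at 98%, only 60 × 0.02 = 1.2 classes are expected not to deliver.

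**Sensitivity to the assumptions.** Other settings, including 4 classes per school and item rates of 50% each or 70%, 80% and 30%, give 4% to 6% at full delivery, 5% to 10% at 98%, 8% to 18% at 95%, 11% to 26% at 90% and 14% to 36% at 80%. Fitted ordinal logit models (300 replications each) give 4.7%, 15% and 23% at 98%, 90% and 80%.

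**School effect on the other items.** With every class delivering the component, a school SD of 0.3 on the logit scale for the other three items gives about 19% rejection. Under other item rates, SDs of 0.2, 0.3 and 0.5 give 14%, 23% and 37%.

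**Analysis at the randomised unit.** A t-test on school mean ranks with 28 degrees of freedom rejects 3.9% to 6.5% of the time across these scenarios, which is nominal within simulation error.

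**The case against.** A reader might infer that the protocol has settled on an unclustered analysis. It has not. The abstract's sentence covers ordinal regression on the primary outcomes, and adherence is the only outcome that the analysis section assigns an ordinal model, so clustering is at least conditionally linked to it. Nor does assessment on the individual level mean that clustering is ignored, since the same phrase covers responsiveness, which then gets a mixed model. This stands: the fault is an inconsistent and conditional specification whose operative sentence omits clustering.

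A reader might also infer that the shared item by itself makes the test reject far above 5%. That does not follow. The item is a bare yes/no, dose is recorded separately, and the Background reports high classroom fidelity in the first two trials. Delivery near 100% is therefore possible, and then the item adds little or nothing. The school SDs used above are also assumptions.

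Nor does the power section show that clustering was ignored for adherence, as the working explains.

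Finally, a detailed analysis plan is announced. A municipality term, covariates, class-level intercepts and the degrees-of-freedom method can properly wait for it, and their absence here is no fault. That does not remove the point, because the article does name a model for this outcome and, as written, the model does not fit the design.

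**Conclusion.** The point holds as a specification fault in the analysis of a primary outcome, with a conditional consequence. The adherence sentence names no clustering method, the sentence beside it does for the other primary outcome, and nothing elsewhere makes clustering unconditional for adherence.

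If the sentence is followed literally, the type I error ranges from nominal to several times nominal. It stays near 5% to 7% only if almost every class delivers the component and nothing else varies by school. It reaches about 14% to 36% at 95% down to 70% delivery, or about one in five with a modest school effect at full delivery. The direction follows from the design. The size rests on assumed delivery rates, item rates, class numbers and school effects, none of which the protocol states.

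**What to change.** In the statistical analysis section, specify for adherence an ordinal model that accounts for school clustering: a cumulative-logit model with a random school intercept, or GEE or a school-level analysis, with inference suited to 30 schools. Of these, only the school-level test was checked above. The small-sample behaviour of a mixed ordinal model or GEE should be confirmed before it is adopted.

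In the abstract, make the clustering statement unconditional for the primary between-group comparisons. The qualifier can remain for outcomes with essentially one respondent per school, such as the principals' readiness score at a single time point. Municipality, covariates and the exact degrees-of-freedom method can be left to the analysis plan.

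The cost is a few words and wider intervals. As an illustration from the table, the standard error grows by √1.95 ≈ 1.4 at 95% delivery. Power for adherence should be restated with the ICC and category probabilities used, so that a reader can see whether the stated figures already include this.

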### Setting of the study

Eight municipalities in the Stockholm Region, Sweden, which had previously shown interest in the HSS program were contacted during the fall of 2020 to inquire about their willingness to take part in the IMPROVE study. Information meetings were held between the research team and key personnel such as central administrators and coordinators of school health care to create interest by explaining the rationale and background to the HSS. Two municipalities finally accepted this invitation after discussing it with their education administration. These municipalities had 110,000 and 50,000 inhabitants respectively, with mixed socioeconomy.

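### Schools are randomised within municipality, but the stated primary models do not name municipality; if the municipalities differ, a clustered analysis without it is conservative and loses some power

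*Protocol article*

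**What the plan says.** Under Randomisation and blinding, the protocol article states: "Within each municipality, schools will be randomised 1:1 to group 1" (Basic) or group 2 (Enhanced). The abstract gives the number of clusters: "Thirty schools in two municipalities will participate in the study". How many schools lie in each municipality is not stated. Setting of the study says of the two places: "These municipalities had 110,000 and 50,000 inhabitants respectively, with mixed socioeconomy".

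Under Data management and statistical analysis, the primary models are given in one sentence each: "Between-group effects in the adherence score (0–4) will be analyzed using ordinal logistic regression", and "Between-group effects in the responsiveness score (4-20) will be analyzed using mixed linear regression". The factors listed straight after these, as potential moderators of fidelity, are "school size, fidelity to implementation strategies, baseline organisational readiness, parent educational level and country of birth". Municipality is not among them. The only general statement on adjustment is in the abstract, where the regressions are described as "taking clustering and covariates into consideration where needed". The article also promises a detailed statistical analysis plan before data analysis starts.

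**The concern.** When allocation is balanced within strata, a difference between strata cancels out of the group contrast, so the contrast is more precise than under unrestricted randomisation. The analysis reports that precision only if the stratum is in the model. If it is left out, the municipality difference stays in the estimated between-school variance and the standard error is too large. Adding a school random effect does not cure this, because that effect is where the municipality difference ends up.

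With 30 schools the between-school variance largely determines precision, so the point is not purely formal. The article also gives reason to think that municipality could matter for fidelity. Table 1 has a municipality-level domain of implementation determinants, which includes local policy and cooperation between agencies, and the stakeholder workshops were held separately in each municipality. At stake are intervals that are wider than the design warrants, and a choice about adjustment left open until after the data are in.

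**Working it through.** **1. The plan's own power figure.** For responsiveness, Sample size and power calculation uses 400 parents per group, SD 8 and differences of 0.8, 1.6 and 3.2. A two-sample formula with two-sided α = 0.05 (assumed; not stated) is power = Φ(δ / (SD·√(2/400)) − 1.96).
- δ = 1.6: 1.6 / (8 × 0.0707) = 2.83, and Φ(0.87) = 0.807.
- All three: 0.293, 0.807 and 1.000, against the stated 0.29, 0.81 and 0.99.

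The stated figures therefore match a calculation with no allowance for school or municipality, and do not bear on this point. The adherence power cannot be reproduced, because the category distribution is not given.

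**2. Inputs for the check.**
- From the article: 30 schools, two strata, 1:1 within stratum; effect 1.6/8 = 0.2 SD; 800/30 ≈ 27 parents per school.
- Assumed: split 20/10 (also 16/14); ICC within municipality 0.05 (range 0.01 to 0.10); municipality difference g from 0 to 0.5 SD.

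**3. Size of the standard-error inflation.** At ICC 0.05 the variance of a school mean within municipality is 0.05 + 0.95/27 = 0.0852. With 10 + 5 schools in each arm, the unmodelled difference adds a sum of squares of g² × 2 × (10 × 5/15) = 6.667g² to the residual on 28 degrees of freedom, so the estimated variance has mean 0.0852 + 0.238g².
- g = 0.1: 0.0852 + 0.0024; standard error about 1% too large.
- g = 0.2: 0.0852 + 0.0095; about 5% too large.
- g = 0.3: 0.0852 + 0.0214; about 12% too large.

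**4. Simulation of school means** (equivalent to a mixed model with equal cluster sizes), 20,000 replicates, split 20/10, ICC 0.05:

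| Municipality difference (SD) | Type I without term | Type I with term | Power without term | Power with term |
|---|---|---|---|---|
| 0 | 0.048 | 0.049 | 0.438 | 0.439 |
| 0.1 | 0.048 | 0.050 | 0.429 | 0.436 |
| 0.2 | 0.038 | 0.048 | 0.399 | 0.438 |
| 0.3 | 0.030 | 0.047 | 0.355 | 0.445 |
| 0.5 | 0.012 | 0.051 | 0.232 | 0.437 |

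Power with the term does not depend on g; its average over the five rows is 0.439. Against that, the losses are about 0, 1, 4 and 8 points at 0, 0.1, 0.2 and 0.3 SD. Over ICC 0.01 to 0.10 and both splits, the loss is 0 to 2 points at 0.1 SD, about 2 to 8 at 0.2 SD and about 5 to 17 at 0.3 SD. It is largest at the smallest ICC.

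**5. If no school effect is fitted.** The linear analogue of a single-level model without municipality has type I error of about 0.07 to 0.08 at ICC 0.01, 0.19 at 0.05 and 0.30 at 0.10. No ordinal model was simulated.

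**The case against.** The strongest objection is that this argues from silence. The article is condensed, it promises a detailed analysis plan, and it leaves covariates open. The two model sentences name a regression family and nothing else, neither random nor fixed effects. The list of five factors concerns effect modification, so a stratum's absence from it does not show that the stratum is excluded from adjustment. The harm also needs a municipality difference that the article does not report; both places are described as socioeconomically mixed.

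Most of this stands, and it limits the point. A reader might infer that the blocking is ignored and that both primary tests are therefore conservative. The text does not support that. Municipality is not named, which is not the same as excluded. The conservative direction also needs a school effect in the model, which the ordinal sentence does not mention; without one, the error runs the other way.

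A reader might also arrive at much larger losses by fixing the total ICC at 0.05 and giving municipality 25, 50 or 75% of it: power 0.43, 0.42 and 0.41 without the term against 0.50, 0.58 and 0.68 with it. Those shares imply gaps of √(share × 0.05 / (2/9)) = 0.24, 0.34 and 0.41 SD, or 1.9, 2.7 and 3.3 points at SD 8. All exceed the 1.6-point effect under test, and nothing in the article supports gaps of that size.

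What the objection does not remove is that the need for the term is settled by the randomisation scheme, and need not wait for a later judgement on covariates.

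**Conclusion.** The point holds in a limited form. The article fixes municipality as a randomisation stratum and then states its primary models without it, leaving its inclusion open. In a model with a school effect, omission costs precision rather than validity: type I error stays at or below nominal. Under the base assumptions the power loss is negligible up to a 0.1 SD difference, about 4 points at 0.2 SD and about 8 points at 0.3 SD, where type I error is about 3%. With no difference there is no loss. These sizes rest on an assumed ICC, split and municipality difference, and on a linear model; for the ordinal outcome only the direction carries over, and only once school clustering is modelled. The change is worth making because it costs almost nothing and removes a choice that could otherwise be made after seeing the data.

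**What to change.** In Data management and statistical analysis (and in the analysis plan to come), state that both primary models, adherence and responsiveness, at 12 and at 24 months, include municipality as a fixed effect because randomisation was done within municipality, alongside a school-level clustering term. State the same for the between-group secondary models. Naming the school term for the ordinal model matters as much as naming municipality, since without it that test would be anti-conservative.

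Cost: one sentence, no new data (municipality is known for every school), and one school-level degree of freedom, from 30 − 2 = 28 to 27. If the municipalities do not differ, power is essentially unchanged at 0.44.
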